### Implementation {16c}

All participants will be self-referred. Participants will be enrolled and assigned to trial groups by different study team members (Fig. 1).

**Fig. 1 Fig1:**
[figure not shown]
CONSORT diagram

## Assignment of interventions: blinding

### Who will be blinded {17a}

Due to the nature of the psychological intervention no one from the participants and study team members will be blinded after assignment to intervention. Only data analysts will be blinded to the study groups until all data analyses are completed.

### Procedure for unblinding if needed {17b}

Not applicable because no one will be blinded.

## Data collection and management

### Plans for assessment and collection of outcomes {18a}

Data will be collected at pre-randomization, termination, and 3-, 12-, and 24-month follow-ups. All questionnaires will be self-report and administered online. To ensure collected data is complete and accurate, the online questionnaires will be coded in a way that requires participants to fully answer the questions in order to submit the answers. For a full timeline of questionnaire dissemination, see Table 1.

#### Primary outcomes

Depression symptoms will be measured with the Patient Health Questionnaire (PHQ-9) [29] and Geriatric Depression Scale (GDS) [30]. On the PHQ-9, total scores range from 0 to 27, and a score of four or less indicates no depression, while scores from 5 to 9 points are considered to reflect sub-clinical depression. On the GDS, scores can range between 0 and 15. A score of five or less is considered within the normal range.

#### Secondary outcomes

In addition to symptoms of depression, symptoms of anxiety and general well-being will be measured. The Generalized Anxiety Scale (GAD-7) [31] is a 7-item scale with total scores ranging from 0 to 21. Scores above 10 warrant further investigation of generalized anxiety disorder. The World Health Organization Well-being Index [32] is a 5-item questionnaire. Respondents are asked to rate how they felt during the past two weeks by choosing the best corresponding answer using a 6-item Likert scale where a score of 0 indicates ‘At no time’ and a score of 5—‘All the time’. A higher score indicates greater well-being.

### Plans to promote participant retention and complete follow-up {18b}

All participants will be informed in the informed consent about follow-up assessments. If participants discontinue or deviate from intervention protocols, they will be contacted and study team members will first try to address any concerns participants might have that are altering their adherence to the intervention protocols. In case these concerns cannot be resolved, participants will then be asked to fill in follow-up self-assessment questionnaires online.

### Data management {19}

Most of the data gathered online and saved to a database will be coded automatically. Only a small fraction of demographic data will need to be coded. Data will be stored on a secure server and, after the termination of the study, uploaded to MIDAS, a secure national scientific data repository, where it will be available upon request to corresponding author after reports are published.

### Confidentiality {27}

After giving informed consent, potential and enrolled participants will be asked to provide their email address and telephone number. The platform generates a unique code for each registered individual and stores it on a secure server available only to the research team with administrative rights after logging. Only non-personal data will be available from the data repository after the trial.

### Plans for collection, laboratory evaluation and storage of biological specimens for genetic or molecular analysis in this trial/future use {33}

Not applicable, no samples collected.

## Statistical methods

### Statistical methods for primary and secondary outcomes {20a}

Effect sizes for pre- to post-treatment and between-group comparisons for the main and secondary outcomes will be calculated to evaluate the effectiveness of the intervention. Additionally, regression analysis will be performed to test if treatment expectations prior to the beginning of the treatment predict primary and secondary outcomes.

### Interim analyses {21b}

No interim analysis is planned in this trial.

### Methods for additional analyses (e.g., subgroup analyses) {20b}

Not applicable, subgroup analyses are not planned.

### Methods in analysis to handle protocol non-adherence and any statistical methods to handle missing data {20c}

Initially, intention-to-treat (ITT) analysis will be performed on all primary outcomes in case of drop-out from the study. Secondary per protocol analyses (PPA) will be performed for those participants who adhered to treatment protocol. In ITT analysis last value carried forward will be used to fill in missing data. In PPA analysis missing cases will be removed on a case-by-case basis and only completed data will be analyzed.

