#### Intervention description {11a}

Eligible participants will be randomly assigned at a ratio of 1:1 either to a modular cognitive behavioral therapy group with minimal therapist support or a waiting list control group. Participants in the intervention group will receive access for 8 weeks to a tailored modular ICBT. Participants in the waiting list control group will be instructed to wait for 8 weeks before being able to access the intervention. This intervention was originally developed in Sweden and then translated and adapted for the Lithuanian population. A waiting list control group was chosen as a comparator because no other standardized Internet-based intervention for treatment of depression is available in Lithuanian language at this point in time.

All participants will receive the same first (introduction/rationale) and the last (relapse prevention) modules. The remaining modules will be tailored according to the participant’s condition and preferences. Tailoring will be done by selecting any 6 of the following 10 modules: behavioral activation (parts 1 and 2), acceptance, sleep disturbances, worry and anxiety, loneliness, pain, applied relaxation, the nature of emotions, and a life-review module. The intervention is constructed so that most modules begin with some psychoeducation, followed by exercises for participants to practice with and questions about the material presented in the module. Completed exercises and answered questions are then saved and can be assessed by the therapist. The therapists will assess the assignments, provide feedback, and prescribe modules weekly.

A group of three clinical psychologists and two graduate students of clinical psychology will be involved as therapists in this study. Supervision will be provided regularly by a clinical psychologist with experience in CBT and clinical work with patients suffering from anxiety and depression as well as Internet-delivered treatments.

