#### Strategies to improve adherence to interventions {11c}

Adherence to the intervention will be monitored through the treatment platform. The platform automatically records participant engagement with the intervention. Recorded activity includes login times, module completion, exercise completion, and number of messages sent to the therapist.

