#### Relevant concomitant care permitted or prohibited during the trial {11d}

Ongoing psychopharmacological medications with stable dosage are allowed. Participation in other psychological interventions is prohibited but will not result in withdrawal from the study if started after the intervention. After termination, all participants will be asked about receiving any other intervention during the trial and this information will be reported.

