### Sample size {14}

A power calculation was conducted using GLIMMPLSE software, which is helpful for sample-size calculation for repeated measures and longitudinal studies [33]. Statistical power was set to 0.8, including pre- and post-treatment repeated measurement points; an *α* was set at 0.05. A total sample of 70 participants was needed to reach 80% power. Factoring in an estimated dropout rate of 10% we seek to randomize 78 participants (39 participants in each group). The power analysis is based on the primary outcome variable’s Patient Health Questionnaire (PHQ-9) [29] means and standard deviations of the two time points data based on the results from a similar unpublished study from Sweden (intervention group pre-treatment (T1) *M* = 12.45, *SD* = 4.38, post-treatment (T2) *M* = 6.57, *SD* = 4.34, control group T1 *M* = 14.22, *SD* = 4.19, T2 *M* = 8.11 *SD* = 4.92), with a 1:1 allocation ratio.

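### Any between-arm per-protocol contrast would select on module adherence, which only the ICBT arm can show before crossover, so it is at risk of bias, plausibly but not certainly favouring treatment

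*Protocol article*

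**What the plan says.** The section on non-adherence and missing data {20c} of the protocol article puts intention to treat first: "Initially, intention-to-treat (ITT) analysis will be performed on all primary outcomes in case of drop-out from the study". Gaps in that analysis are filled from earlier values: "In ITT analysis last value carried forward will be used to fill in missing data". The per-protocol analysis follows: "Secondary per protocol analyses (PPA) will be performed for those participants who adhered to treatment protocol". Its rule for missing data is different: "In PPA analysis missing cases will be removed on a case-by-case basis and only completed data will be analyzed".

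Three other sections decide what adherence can mean in each arm.

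- Intervention description {11a}, on the controls: "Participants in the waiting list control group will be instructed to wait for 8 weeks before being able to access the intervention".
- Strategies to improve adherence {11c}, on what the platform logs: "Recorded activity includes login times, module completion, exercise completion, and number of messages sent to the therapist".
- Concomitant care {11d}, on a deviation that could occur in either arm: "Participation in other psychological interventions is prohibited but will not result in withdrawal from the study if started after the intervention".

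Outcomes {12} and Statistical methods {20a} plan both within-group and between-group effects. Section {20c} does not say which of these the per-protocol analysis covers.

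**The concern.** Before crossover a waiting-list participant has no modules to complete, and the adherence record described is use of the programme. On the natural reading, low users are removed from the ICBT arm and the rest are compared with a largely intact waiting list. Whoever is removed is identified by conduct after randomisation, so the two groups compared are no longer the randomised groups. Setting an adherence cut-off does not cure this, because it only moves the line along which one arm is selected.

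If people who work through modules would have done better anyway, the contrast credits that advantage to the programme. The practical stake is how the two results would be read side by side. For a simple two-sided comparison of post-treatment means, with the planning difference of 1.54 points and SD 4.64, power at 35 per arm is about 28%. An inconclusive intention-to-treat result beside a more favourable adherer result is therefore a realistic outcome, and section {20c} does not say which governs if they differ.

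**Working it through.** The article gives no figure for the per-protocol analysis, so there is none to reproduce.

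**Inputs from Sample size {14}**

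- Randomised: 70 / (1 − 0.10) = 77.8, rounded up to 78, which agrees with the article; 39 per arm.
- Post-treatment PHQ-9: intervention mean 6.57 (SD 4.34), control mean 8.11 (SD 4.92). Difference: 8.11 − 6.57 = 1.54 points.
- Pooled SD: √[(4.34² + 4.92²) / 2] = √21.52 = 4.64.

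**Inputs assumed, because the article gives neither**

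- Share *e* of the ICBT arm excluded: 10% or 30%.
- Gap *g* by which those excluded would, untreated, have done worse than adherers: 0.3 or 0.5 SD.

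**Formula.** With no treatment effect, the whole arm's mean is (1 − *e*) × adherer mean + *e* × non-adherer mean. The adherer mean therefore differs from the whole-arm mean by *e* × *g*. If the waiting list is kept whole, that is the bias.

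| Excluded | Gap (SD) | Bias (SD) | Bias (points, × 4.64) | Share of 1.54 | Two-sided rejection at nominal 5%, no true effect |
|---|---|---|---|---|---|
| 10% (35 v 39) | 0.3 | 0.03 | 0.14 | 9% | 5.2% |
| 10% (35 v 39) | 0.5 | 0.05 | 0.23 | 15% | 5.5% |
| 30% (27 v 39) | 0.3 | 0.09 | 0.42 | 27% | 6.4% |
| 30% (27 v 39) | 0.5 | 0.15 | 0.70 | 45% | 9.1% |

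The arm sizes are 39 × 0.90 ≈ 35 and 39 × 0.70 ≈ 27. All 39 controls are kept, although complete-case deletion would remove some.

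**Check with a second selection model.** Let adherence depend on a latent normal variable with correlation ρ to a better outcome, and let a share *p* adhere. With no true effect the bias is −ρ × 4.64 × φ(z) / *p*, where φ is the standard normal density and z is the point that the latent variable exceeds with probability *p*. Negative values favour treatment.

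| ρ (assumed) | *p* = 90% | *p* = 70% | *p* = 50% |
|---|---|---|---|
| 0.5 | −0.45 | −1.15 | −1.85 |
| 0.3 | −0.27 | −0.69 | −1.11 |
| 0 | 0 | 0 | 0 |
| −0.3 | +0.27 | +0.69 | +1.11 |

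The row for ρ = −0.3 is the case in which people who improve early stop using modules. Neither the sign nor the size is fixed by anything in the article.

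Deleting missing cases has no separate calculation. Its effect depends on who is missing and in which arm, and the article gives no basis for a figure.

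**The case against.** A secondary per-protocol analysis beside intention to treat is conventional, and this one is labelled secondary. Nothing in the article makes it the evidence of effectiveness; the Abstract also assigns the primary outcomes to intention to treat. That stands, and it limits how much the point matters.

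A reader might infer that the contrast is biased in favour of treatment. The article has no evidence on the prognosis of adherers, and the second table shows zero and reversed bias under assumptions that cannot be ruled out. Only a risk of bias is supported.

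A reader might also infer that the waiting list is certain to be kept whole. Section {11d} prohibits other psychological treatment, so some controls could be excluded, and complete-case deletion applies to both arms. This stands too, but excluding controls on a different criterion would not make the remaining groups comparable.

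The per-protocol analysis may be only a within-group description, since section {20c} does not say. The point therefore applies to any between-arm version. Nor is the absence of an adherence threshold a fault here, since that is commonly left to an analysis plan.

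Finally, the larger figures rest on an assumed 30% exclusion. The only attrition figure given is 10% dropout. Dropout is not the same as non-adherence, but at 10% excluded the rejection rate stays close to nominal.

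**Conclusion.** The point holds as a minor one. Before crossover, module adherence can exist only in the ICBT arm, so a between-arm comparison of adherers with the waiting list is not protected by randomisation and does not estimate the effect of adhering. The bias plausibly, but not certainly, favours treatment.

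Its size is unknown. In the illustration it runs from about 9% to 45% of the 1.54-point planning difference. This rests on the assumed exclusion shares and prognostic gap, a waiting list kept whole, and the SD from the unpublished Swedish study used for planning.

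The document does not support reading this as a flaw in the trial's main conclusion, because intention to treat leads.

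**What to change.** 1. State that the conclusion on effectiveness rests on the intention-to-treat analysis, whatever the adherer analysis shows.
2. Replace any between-arm adherer contrast with a complier-average causal effect at the post-treatment assessment, using randomisation as the instrument. Non-adherence is one-sided at that point because the waiting list does not yet have access. Define adherence from the platform's module-completion record, with a threshold fixed before analysis.
3. Report adherers' outcomes descriptively, within the ICBT arm only.

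The cost is a little extra analysis on data the platform already records. Three limits should be stated with the result.

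- The complier estimate is less precise.
- It is essentially the intention-to-treat effect divided by the adherence share, so it adds no independent evidence of efficacy. At an assumed 70% adherence, 1.54 becomes 1.54 / 0.70 = 2.20 points.
- It assumes no benefit below the threshold. If partial users of a modular programme benefit, it overstates the effect.

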**Methods:**

A minimum of 60 participants will be recruited and randomly assigned to groups in a two-armed parallel controlled trial with a waiting list. The intervention group will have access to an 8-week therapist-supported modular intervention. The waiting list group will be instructed to wait for 8 weeks and then granted access to the intervention for 8 weeks. Pre, post, and 3-, 12-, and 24-month follow-up assessments are planned for measuring changes in depression symptoms, anxiety symptoms, and psychological well-being using PHQ-9, GDS, GAD-7, and WHO-5. Primary outcomes of all the participants will be analyzed using the intention-to-treat principle, and within- and between-group effect sizes will be calculated.

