## Objectives {7}

The aim of this study is to test the effectiveness of an Internet-based cognitive behavioral therapy with minimal therapist support for depressed older adults. Our hypothesis is that the treatment group will have significantly larger reductions in symptoms of depression when compared to the waiting list control group post-treatment and will retain these effects at the 3-month follow-up. We will further seek to evaluate retention at 12- and 24-month follow-ups.

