### Outcomes {12}

Difference between intervention and control groups pre- and post-treatment as well as at 3-month and 1- and 2-year follow-ups will be analyzed for both primary and secondary outcomes. Primary outcomes are depression symptoms measured with the Patient Health Questionnaire (PHQ-9) [29] and Geriatric Depression Scale (GDS) [30]. Secondary outcomes include anxiety symptoms and psychological well-being. Anxiety symptoms will be measured with the Generalized Anxiety Disorder Scale (GAD-7) [31] and levels of psychological well-being will be measured with the World Health Organization Well-being Index (WHO-5) [32]. Difference in means post-treatment will be compared between groups for both primary and secondary outcomes. Within group trial effects will be calculated using difference in means from baseline to post-treatment for all primary and secondary outcomes. Additionally long-term effectiveness of the intervention will be measured comparing outcome differences from post-treatment to 3-month and 1- and 2-year follow-ups.

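### Carrying the last value forward in the ITT analysis scores every post-treatment dropout as unchanged from baseline and pulls follow-up change towards zero

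*Protocol article*

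**What the plan says.** Section {20c} fixes the method: "In ITT analysis last value carried forward will be used to fill in missing data". The same section introduces ITT with "intention-to-treat (ITT) analysis will be performed on all primary outcomes in case of drop-out from the study". The only other analysis of incomplete data is per protocol: "In PPA analysis missing cases will be removed on a case-by-case basis and only completed data will be analyzed". No other missing-data method or sensitivity analysis is named.

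Section {18a} gives the assessment times: "Data will be collected at pre-randomization, termination, and 3-, 12-, and 24-month follow-ups". Table 1 agrees. PHQ-9 and GDS appear at baseline, at t9 (post) and at the three follow-ups, with nothing in the weekly t1–t8 column.

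The Objectives section predicts that the treatment group "will retain these effects at the 3-month follow-up". Outcomes {12} measures long-term effectiveness by "comparing outcome differences from post-treatment to 3-month and 1- and 2-year follow-ups". The Abstract adds: "The waiting list group will be instructed to wait for 8 weeks and then granted access to the intervention for 8 weeks". Sample size {14} allows for dropout once, for the whole trial: "Factoring in an estimated dropout rate of 10" per cent.

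**The concern.** Carrying a value forward assumes that a participant's score stops moving once it is no longer observed. In this schedule that means two different things.

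- **At t9** the only earlier score is baseline, so each missing participant is recorded as having gained nothing. The protocol's planning data show large falls in both arms, so this is a poor guess for either arm. The treatment contrast is then distorted by an amount that depends on how many are missing from each arm.
- **At follow-up** the carried score is normally the t9 score, so each missing participant is recorded as having neither relapsed nor improved since treatment ended. That is the pattern the retention hypothesis predicts.

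Filled-in scores are also analysed as if they had been observed. The completers-only per-protocol analysis is no safeguard, because it selects on adherence and completion. At stake are the main ITT estimate and the retention claim.

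**Working it through.** **Inputs from the protocol (Sample size {14}).** 70 evaluable participants, 10% dropout, 1:1 allocation. PHQ-9 means: intervention 12.45 to 6.57, control 14.22 to 8.11.

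**Assumed, because not given.** Dropout by arm, follow-up attrition, pre–post correlation (0.5) and the test (baseline-adjusted ANCOVA). Missingness is taken as unrelated to outcome.

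**1. The plan's own dropout figure.** 70 / (1 − 0.10) = 77.8, rounded up to 78, or 39 per arm. This agrees with the protocol. How the 70 was reached is a separate question and does not enter below.

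**2. Improvement in the planning data.** Intervention 12.45 − 6.57 = 5.88. Control 14.22 − 8.11 = 6.11. Scoring a missing t9 as no change is therefore wrong by about 6 points on average in either arm, if this trial behaves like the planning study.

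**3. Post-treatment contrast with carried values.** Let C be the mean reduction and d the share missing (i = intervention, c = control; positive favours the intervention):

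estimate = Ci(1 − di) − Cc(1 − dc).

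- Equal dropout d: estimate = (1 − d)(Ci − Cc). With d = 0.10 and a true effect of 3.0, this is 0.9 × 3.0 = 2.7.
- No true effect, common improvement C: estimate = C(dc − di). With C = 6.11 this is 0.061 points per percentage point of imbalance; with C = 2 it is 0.02.
- No true effect, dropout 20% v 10% (intervention v control): 6.11 × (0.10 − 0.20) = −0.61; with C = 2, −0.20. Reversing the arms reverses the sign.
- True effect 3.0, dropout 20% v 10%: with C = 6.11, 9.11 × 0.8 − 6.11 × 0.9 = 7.29 − 5.50 = 1.79; with C = 2, 5 × 0.8 − 2 × 0.9 = 2.20.

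**4. Error rates by simulation** (39 per arm, SD 4.5, correlation 0.5, ANCOVA, two-sided 5%):

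| Dropout (intervention v control) | Common improvement | True effect | Carried-forward result | Observed data |
|---|---|---|---|---|
| 10% v 10% | 6.11 | 0 | type I error about 5% | about 5% |
| 20% v 10%, or reversed | 6.11 | 0 | type I error about 9–10% | about 5% |
| 30% v 10% | 6.11 | 0 | bias 1.2, type I error about 23% | about 5% |
| 20% v 10% | 2 | 0 | type I error about 6% | about 5% |
| 30% v 10% | 2 | 0 | bias 0.4, type I error about 8% | about 5% |
| 10% v 10% | 6.11 | 3.0 | estimate 2.7, power 75–77% | estimate 3.0, power 88–89% |
| 20% v 10% | 6.11 | 3.0 | estimate 1.8, power 37–39% | estimate 3.0, power about 87% |
| 20% v 10% | 2 | 3.0 | estimate 2.2, power 68% | – |

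A t-test on change gives the same picture. With a true effect of 3.1, 6.11 points of common improvement and 10% missing in both arms, carried values give 2.79 and power 71%, against 3.10 and 81% with observed data.

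**5. Follow-up.** With t9 observed and a fraction m missing later, each carried value contributes a change of exactly 0, so

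estimated change = (1 − m) × true change.

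A true relapse of 3.0 points out of a 5.88-point gain leaves (5.88 − 3.0)/5.88 = 49% of the gain. Over an assumed range of m:

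| m | Apparent relapse | Apparent gain kept |
|---|---|---|
| 10% | 2.7 | 54% |
| 20% | 2.4 | 59% |
| 30% | 2.1 | 64% |
| 50% | 1.5 | 74% |

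**6. Waiting list at follow-up.** These participants receive the programme after week 8. A t9 score carried to a later visit is therefore an untreated score standing in for a treated one. If treatment works, this tilts any between-group comparison at follow-up towards the intervention arm.

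**The case against.** - **The planned case is mild.** The protocol expects 10% dropout and does not predict a difference between arms. If dropout is equal, the post-treatment bias is towards no effect and type I error is unaffected. This stands. A reader might infer that the method inflates type I error in general; the documents do not support that, because inflation needs differential dropout. Imbalance is nonetheless plausible in an unblinded trial where one arm works through weekly modules and the other waits.
- **The 6.11 points may not apply.** They come from the control arm of an unpublished study, and the protocol does not describe that control condition. If waiting-list participants here improve by only 2 points, the distortion under imbalance is much smaller. This stands too, and is why both values are shown.
- **The comparator is favoured.** Missingness was simulated as unrelated to outcome, so the observed-data analysis is unbiased by construction, and the protocol does not name the test. True, but the formulas in steps 3 and 5 do not depend on the test.
- **Retention is not built in.** A reader might infer that carrying values forward makes the retained-effects finding certain. It does not: only the missing share is pulled to zero change, and observed participants still show their relapse.
- **Secondary outcomes.** Because ITT is stated for the primary outcomes, a reader might infer that GAD-7 and WHO-5 are left to the per-protocol set. Section {20c} does not say so; it calls the per-protocol analyses secondary and does not assign secondary outcomes to them.
- **Mitigation and purpose.** Participants who discontinue are still asked for follow-up questionnaires ({18b}), online forms cannot be submitted incomplete ({18a}), and the trial is labelled exploratory ({8}). These should reduce the amount missing and temper the consequences, but they do not change how the remaining missing scores are treated.

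**Conclusion.** The concern holds. The method is fixed in the protocol, and with this assessment schedule it becomes baseline carried forward at t9 and, normally, t9 carried forward afterwards.

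- **At the planned 10% dropout, equal by arm:** a true effect is shrunk by about 10%. Power falls by roughly 12 percentage points for a 3.0-point effect with 6.11 points of common improvement. Type I error stays near 5%.
- **If dropout differs by arm (an assumption):** the bias can go either way. With no true effect and 20% v 10% dropout it is 0.6 points with type I error about 9–10% at 6.11 points of common improvement, and 0.2 points with about 6% at 2 points.
- **At follow-up:** change since treatment is understated by whatever fraction is missing, in the direction of the retention hypothesis. The protocol gives no follow-up attrition, so the size cannot be fixed from the document.

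The power and error rates also rest on a correlation of 0.5, an SD of 4.5 and missingness unrelated to outcome.

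**What to change.** Replace last value carried forward in section {20c} with a likelihood-based mixed model for repeated measures, or multiple imputation that includes the baseline score, using all observed data from all randomised participants. Estimate the change from post-treatment to each follow-up from the same model, with nothing carried forward. Add a sensitivity analysis in which dropouts are assumed to do worse than the model predicts. If last value carried forward is kept at all, label it as a sensitivity analysis.

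The cost is a change of wording and a little programming; no extra data are needed. The price is reliance on data being missing at random, which the added sensitivity analysis probes.
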